### Randomization Procedure

Participants will be randomized immediately prior to surgery using a computer-generated randomization sequence, in accordance with CONSORT guidelines. Patients will be assigned to one of two groups:Control Group: Umbilical trocar site closure will be performed using the standard technique (continuous suture).Study Group: A reinforcing intraperitoneal mesh will be placed at the umbilical trocar site following continuous suturing.

### Intervention

The umbilical port will be inserted using the Hasson technique, which requires a transverse incision of aponeurosis. The placement and insertion of additional trocars will be at the discretion of the operating surgeon. The laparoscopic cholecystectomy will be performed in a standard fashion, with the specimen extracted via the umbilical trocar site using an endoscopic retrieval bag. If necessary, the incision may be extended, and the final length of the aponeurotic incision will be recorded.

In the control group, aponeurotic closure will be performed using a continuous suture with 0 polydioxanone. In the study group, a reinforcing mesh will be placed in an intraperitoneal sublay position, and the same continuous 0 polydioxanone suture will be used for mesh fixation. A 4.3 cm composite mesh (Ventralex™ ST Hernia Patch, Bard Davol, New Jersey, USA) will be used in the study group. This mesh consists of an anterior layer of polypropylene monofilament and a posterior absorbable hydrogel barrier, which permits safe contact with the peritoneal cavity. The intraperitoneal sublay position allows for a reduction in surgical time required for mesh placement.

Both groups will receive a single dose of 2 g of cefazolin preoperatively. Local anesthesia will be administered at all trocar insertion sites.

### Follow-Up

Postoperative follow-up will be carried out at 30 days, 6 months, and 1 year after surgery—including abdominal wall ultrasound—and again at 2 years postoperatively.

Each follow-up visit will include assessment of postoperative complications, pain [measured using the Visual Analogue Scale(VAS)], time to return to work, and resumption of daily activities.

### Blinding

The trial is blinded with respect to the principal investigator. Patients are informed about whether a mesh was placed, in accordance with our current protocol. However, the surgeon (principal investigator) remains blinded during follow-up. To maintain blinding, the physical examination must be performed prior to the abdominal wall ultrasound assessment. Subsequently, the ultrasound examination must be conducted by a specialized radiologist.

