### Patient Evaluation and Selection (Inclusion/Exclusion Criteria)

Patient recruitment will be conducted by the surgeon during routine preoperative consultations. The study will be offered to adult patients (aged ≥18 years) scheduled to undergo laparoscopic cholecystectomy who fulfil at least one of the inclusion criteria. The inclusion criteria comprise the following risk factors for trocar incisional hernia: diabetes mellitus, body mass index (BMI) ≥30 kg/m^2^, age ≥65 years, or intraoperative enlargement of the umbilical trocar incision (Figure 1).

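### Examining before scanning cannot keep the examiner blinded at 2 years, the ultrasound reader is outside the stated blind, and the double-blind claim conflicts with telling patients their allocation

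*Protocol article*

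**What the plan says.** The Blinding section of the protocol article limits the blind to one role: "The trial is blinded with respect to the principal investigator". Patients are not blinded: "Patients are informed about whether a mesh was placed, in accordance with our current protocol". The section then states its aim for the examiner, "However, the surgeon (principal investigator) remains blinded during follow-up", and the means of reaching it, "To maintain blinding, the physical examination must be performed prior to the abdominal wall ultrasound assessment". On the scan itself it adds only this: "Subsequently, the ultrasound examination must be conducted by a specialized radiologist".

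The Follow-Up section lists visits at 30 days, 6 months and "1 year after surgery—including abdominal wall ultrasound—and again at 2 years postoperatively". The Abstract attaches the ultrasound to the 1-year visit and places the 2-year visit after it.

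The Data Collection and Analysis section makes hernia at the umbilical port the primary variable and does not say by which modality it is diagnosed. The Introduction defines incisional hernia as a defect found by examination, imaging or both. It adds that a sound diagnosis often needs the two together and that many patients have no symptoms.

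The Discussion describes the trial as double-blind, for patients as well as principal investigators.

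**The concern.** Examining before scanning is a sensible precaution only if the scan can show whether a mesh is present. Once that is granted, three things follow. The precaution expires for any examination made after a scan has been reported. The person reading the scan may see the allocation. And a patient who knows the allocation can reveal it at any visit, whatever the order of procedures.

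Deciding whether there is a defect at a small port site involves judgement. If the threshold for calling a hernia differs between arms because the assessor knows or suspects the allocation, part of the observed difference comes from detection rather than from the mesh. In a trial of 42 per group, a modest difference in detection is enough to change how often a null comparison reaches significance.

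**Working it through.** **Step 1. Does the mechanism deliver the aim?** The passages side by side:

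| Assessment | Does the order rule protect it? | Why |
|---|---|---|
| Clinical examination up to and including 1 year (Abstract schedule) | Yes, apart from disclosure by the patient | No scan has yet been done |
| 1-year ultrasound reading | No | The stated blind covers the principal investigator only, and the rule implies that the scan can show the mesh |
| 2-year clinical examination | No | It follows the 1-year scan, and nothing in the article keeps that report from the examiner |

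The aim covers the whole of follow-up. The mechanism covers only the part before the first scan.

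**Step 2. Does the ultrasound matter to the primary endpoint?** The endpoint sentence names no modality. However, the Introduction allows imaging to establish a hernia and says that diagnosis often needs it, and ultrasound is the only imaging in the visit schedule. That the reading contributes to the endpoint is therefore an inference, though a well-supported one.

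**Step 3. Are the statements on patient blinding consistent?** No. The Blinding section says that patients learn whether they received a mesh, and the Discussion says that patients are blinded.

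**Step 4. How much could unequal detection matter?** This point disputes none of the protocol's figures. The inputs taken from the Sample Size Calculation section are a control rate of 35%, two-sided alpha of 0.05 and 42 per group. The miss rates *m* are assumptions; the document gives none.

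Let the true rate be 35% in both arms, so that there is no real effect. Suppose a fraction *m* of hernias is missed in one arm only.

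- Observed rate in that arm: 0.35 × (1 − m)
- Spurious difference: 0.35 × m
- Test: z = (p1 − p2) / √[p̄(1 − p̄) × 2/n], rejecting when |z| > 1.96, where p̄ is the pooled proportion
- False-positive rate: the sum of the exact binomial probabilities of all pairs of counts that lead to rejection

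| m (assumed) | Observed rate | Spurious difference | False positives, n = 42 | False positives, n = 38 |
|---|---|---|---|---|
| 0 | 35% | 0 | 5.3% | 5.0% |
| 10% | 0.35 × 0.90 = 31.5% | 3.5 points | 6.5% | 6.3% |
| 20% | 0.35 × 0.80 = 28% | 7 points | 10.7% | 10.2% |
| 30% | 0.35 × 0.70 = 24.5% | 10.5 points | 18.4% | 17.4% |

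The last column is included because the protocol says that 42 already allows for 10% loss, which would leave 42 × 0.90 = 37.8, about 38 evaluable. The picture does not change.

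**The case against.** The best defence is that the rule does real work. On the Abstract's schedule it protects every clinical examination up to and including 1 year. Loss of the blind at 2 years also requires the 1-year report to reach the examiner, and the article does not say that it does; a fuller protocol may withhold it. This stands as a limit on the point. It does not remove the point, because the article claims blinding throughout follow-up and rests it on a step that cannot provide it after the first scan.

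The illustration can fairly be called high. If imaging or examination can each establish a hernia, those found at the blinded 1-year examination would still count. If half were found that way (an assumption), missing 20% of the rest is an overall miss of 0.5 × 0.20 = 10%, the 6.5% row. That is why the table gives a range.

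A reader might also infer several stronger things that the document does not support:

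- *The scan is repeated at 30 days and 6 months, so the blind fails at once.* The Follow-Up sentence can be read that way, but the Abstract ties the ultrasound to 1 year.
- *The operating surgeon may be the examiner.* Someone who placed or omitted the mesh could not remain blinded, so the stated aim already excludes that person. The statement "Patient recruitment will be conducted by the surgeon during routine preoperative consultations" concerns recruitment, not follow-up.
- *Other, unblinded examiners work at the second hospital.* None is mentioned, and the Discussion uses the plural for principal investigators.
- *The endpoint is decided throughout by people who know the arm.* This is not so for the examinations before the first scan, unless a patient discloses.
- *The bias favours mesh.* Nothing in the document fixes its direction.

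**Conclusion.** The point holds in a limited form. The only stated mechanism cannot secure the stated blinding at the 2-year examination. The ultrasound reader is outside the stated blind, although the rule itself implies that the scan can reveal the mesh. Patients know their allocation, can disclose it, and are wrongly described as blinded in the Discussion. The first and third of these follow directly from the text. The second matters to the primary endpoint by inference, since no modality is named for it.

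Ascertainment could therefore differ by arm, in either direction and by an unknown amount. Under the assumed miss rates of 10% to 30% in one arm, a true 35% in both arms and 42 evaluable per arm, the spurious difference is 3.5 to 10.5 points and the false-positive rate is 6.5% to 18.4%, against 5.3% with equal detection. These figures show sensitivity and do not predict what will happen. The weakness should be corrected, because it touches the primary endpoint and costs little to repair.

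**What to change.** 1. State that at every visit, including 2 years, the examiner has no access to the operative note or to any ultrasound report, that patients are asked not to disclose their allocation, and that the result is entered in REDCap before those records are opened. For this to hold at 2 years, whoever opens the 1-year report must not be the person who examines at 2 years.
2. Have the radiologist apply one fixed hernia definition in both arms, and state openly that the ultrasound reading is not blinded. Leaving the allocation off the request would not be enough if the scan shows the mesh.
3. Report the blinded 1-year clinical result as a prespecified sensitivity analysis beside the ultrasound-based endpoint.
4. Correct the double-blind statement in the Discussion so that it agrees with the Blinding section.

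The cost is wording and some organisation. Reports have to be kept from the study examiner, and the article has to disclose a weaker blinding claim than it now makes. No treatment, visit or sample size changes.

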### Data Collection and Analysis

The primary variable is the occurrence of herniation at the umbilical trocar site (eventration/TSIH).

Secondary variables include:Biodemographic data: age, sexComorbidities and clinical history: diabetes mellitus, BMI, hypertension, chronic pulmonary disease, cardiovascular disease, immunosuppression, ASA score, smoking statusIntraoperative factors: need for enlargement of the umbilical wound, conversion to open surgeryPostoperative outcomes: surgical site occurrences, pain (measured using the Visual Analogue Scale [VAS]), length of hospital stay, emergency department visits, hospital readmissions, return to work, and resumption of basic activities of daily living

All data will be collected and anonymized through the Research Electronic Data Capture (REDCap ®, Vanderblit University, USA). Access will be restricted to study investigators using individually assigned access credentials.

### Sample Size Calculation

The primary outcome for the sample size calculation is the incidence of umbilical trocar site hernia. Based on published data, the expected incidence of umbilical trocar site hernia in high-risk patients is approximately 35%. The study hypothesises that prophylactic mesh placement will reduce the incidence to 10%; therefore, we assume a 25% reduction.

Assuming a 25% reduction in umbilical trocar site hernia, a two-sided alpha risk of 0.05 and a power of 80% (β < 0.2), and accounting for a 10% dropout or loss to follow-up, the random sample size is 42 patients per group to detect a statistically significant difference between the intervention and control groups.

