**Methods:**

This prospective, multicentre, randomised controlled trial provides Level I evidence. Eligible participants are adults scheduled for laparoscopic cholecystectomy with diabetes mellitus, BMI ≥30 kg/m^2^, age ≥65 years, or requiring umbilical incision enlargement. Patients will be randomised 1:1 to standard aponeurotic closure or intraperitoneal sublay mesh reinforcement (Ventralex™ ST). Follow-up visits are scheduled at 30 days, 6 months, 1 year—with ultrasound—and 2 years. The principal investigator will remain blinded during follow-up. The primary endpoint is TSIH incidence; secondary outcomes include surgical site events, postoperative pain, readmissions, and time to return to daily activities. Based on expected TSIH reduction from 35% to 10%, 42 patients per arm are required.

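### The stated 42 patients per group is not reproduced once the 10% loss is included; with about 38 evaluable per group the power is about 75–78%, not 80%

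*Protocol article*

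**What the plan says.** The protocol article's Sample Size Calculation section gives every input that a two-proportion calculation needs:

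- Control group: "the expected incidence of umbilical trocar site hernia in high-risk patients is approximately 35" per cent.
- Mesh group: the hypothesis is that "prophylactic mesh placement will reduce the incidence to 10" per cent.
- Error rates: "a two-sided alpha risk of 0.05 and a power of 80% (β < 0.2").
- Losses and result: "accounting for a 10% dropout or loss to follow-up, the random sample size is 42 patients per group".

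The abstract gives the allocation ("Patients will be randomised 1:1 to standard aponeurotic closure" or to mesh reinforcement) and repeats the size without mentioning losses: "Based on expected TSIH reduction from 35% to 10%, 42 patients per arm are required". The article names no formula or test, and gives no sample size before losses.

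**The concern.** The article says that 42 per group already contains a 10% allowance for losses. If so, the calculation before losses must have given about 42 × 0.9 = 37.8, or 38, evaluable patients per group. For 35% against 10% at these error rates, that is fewer than the usual formulas require, while 42 itself is about what they require with no losses at all.

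At stake is the stated power. It is the figure against which a non-significant result will be read. If 80% after losses does not follow from the plan's own assumptions, the risk of missing a true effect of the planned size is understated. With 84 patients in total there is little slack to absorb losses.

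**Working it through.** **Inputs.** p1 = 0.35, p2 = 0.10, difference d = 0.25, two-sided alpha 0.05 (z = 1.960), power 80% (z = 0.8416) and 10% loss, all from the Sample Size Calculation section; 1:1 allocation from the abstract. The only assumption added is the formula, so several are tried. The mean proportion is (0.35 + 0.10)/2 = 0.225.

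**Step 1: evaluable patients per group before losses.**

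- Pooled variance under the null: n = [1.960·√(2 × 0.225 × 0.775) + 0.8416·√(0.35 × 0.65 + 0.10 × 0.90)]² / 0.25² = (1.1575 + 0.4742)² / 0.0625 = 42.6, so 43.
- Unpooled: n = (1.960 + 0.8416)² × (0.2275 + 0.0900) / 0.0625 = 7.849 × 0.3175 / 0.0625 = 39.9, so 40.
- Arcsine: h = 2·arcsin√0.35 − 2·arcsin√0.10 = 1.2661 − 0.6435 = 0.6226; n = 2 × 7.849 / 0.3876 = 40.5, so 41.
- Exact enumeration of the uncorrected chi-square test: power is 79.3% at 40 per group and 80.5% at 41, so 41.

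These sizes, 40 to 43, bracket the stated 42 with no losses allowed for.

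**Step 2: add the 10% loss, n/(1 − 0.10).**

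| Method | Evaluable | Randomised |
|---|---|---|
| Unpooled | 40 | 40/0.9 = 44.4 → 45 |
| Arcsine | 41 | 41/0.9 = 45.6 → 46 |
| Exact chi-square | 41 | 41/0.9 = 45.6 → 46 |
| Pooled | 43 | 43/0.9 = 47.8 → 48 |

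None gives 42.

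**Step 3: other routes to 42.**

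- Multiplying by 1.1 instead of dividing by 0.9 gives 40 × 1.1 = 44 at the lowest.
- A one-sided pooled calculation, against the stated two-sided alpha, gives 34 before losses and 34/0.9 = 37.8, so 38, after them.
- Reading the 25% as a relative reduction (35% to 26.25%) would need about 435 per group.

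None of these gives 42 with the loss included.

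**Step 4: power with 42 randomised per group.** Evaluable: 42 × 0.9 = 37.8, about 38.

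- Pooled: (0.25·√38 − 1.1575)/0.5635 = 0.681, power 75.2%.
- Unpooled: 0.25·√38/0.5635 − 1.960 = 0.775, power 78.1%.
- Arcsine: 0.6226·√(38/2) − 1.960 = 0.754, power 77.5%.
- Exact enumeration of the uncorrected chi-square test: 77.0%.

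Against 80%, the shortfall runs from 80 − 78.1 = 1.9 to 80 − 75.2 = 4.8 percentage points.

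**Step 5: power at 42 evaluable, with no losses.** Pooled 79.4%, arcsine 81.4%, exact chi-square 81.6%, unpooled 82.0%. The claim of about 80% fits 42 evaluable patients, not 42 randomised.

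**The case against.** The strongest objection is that the gap is small and depends on the formula. The article names none, and under the unpooled formula the shortfall is only about 2 points. That is minor beside the uncertainty in a planning rate which the article itself calls approximate. The size of the shortfall stands as a reason for proportion: this is a correction to a stated figure, not a flaw in the comparison. It does not rescue the figure, because every formula tried falls below 80% at 38 evaluable and none gives 42 after losses.

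That the article condenses a fuller protocol does not help either. Nothing is said to be missing. The inputs, the allowance and the result are all printed, and they do not agree.

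A reader might infer more than the document supports:

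- *That the dropout allowance was forgotten.* The match with 40 to 43 suggests it, but no size before losses or formula is given, so how 42 arose is unknown. What can be shown is that it is not reproduced.
- *That 80% power holds only if nobody is lost.* This is wrong in both directions. The pooled formula gives 79.4% at 42 even with no losses, while the exact chi-square reaches 80.5% at 41 evaluable and the unpooled formula 80.1% at 40.
- *That the true power is far lower.* Fisher's exact test would have 68.7% power at 38 per group, and a continuity-corrected formula would need 57 randomised. The article mentions neither, so neither can be used to size this gap.
- *That calling the effect a 25% reduction is an error of substance.* The 35% and 10% stand beside it, so the absolute meaning is clear. It is a matter of wording.

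**Conclusion.** The concern holds as an arithmetic error. On the article's own inputs, 80% power needs about 40 to 43 evaluable and, with 10% loss, 45 to 48 randomised per group; the stated 42 falls short of that by 3 to 6 patients per group. With 42 randomised and about 38 evaluable, power is about 75–78%, so the type II error is about 22–25% where the plan states less than 20%.

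This rests on 35% against 10% being the true rates, on equal 10% loss in both groups, and on a two-sided test without continuity correction. The direction holds for every such method tried; only the size of the gap varies. The validity of the primary comparison and its type I error are not in question.

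**What to change.** In the Sample Size Calculation section, replace the claim with wording such as: 42 randomised per group leaves about 38 evaluable after 10% loss and gives about 75–78% power, depending on the formula, for a 25-percentage-point reduction (35% to 10%); about 80% power needs roughly 40–43 evaluable per group. Name the formula used and, once named, give its single power figure in place of the range. Make the abstract's sentence on the required size agree.

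The cost is one sentence in each place and a slightly less favourable stated power; no extra patients are needed. If the sponsor would rather keep 80% after 10% loss, the consistent size is 45 to 48 per group by formula (48 with the pooled one), that is 90 to 96 in total instead of 84.

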## Discussion

Incisional hernia is one of the most frequent complications in open surgery, with a considerable rate of morbidity and mortality. Advances in anatomical knowledge and new technological devices have improved surgical techniques and devices aimed at preventing and treating incisional hernias in open surgery.

In recent decades, there has been a significant increase in laparoscopic surgery. Nowadays, laparoscopic access to the abdominal cavity is considered the gold standard for a large number of procedures. Initially, it was assumed that the laparoscopic approach would drastically reduce the incidence and/or severity of postoperative complications related to incisional hernias. However, it is now well recognized that TSIH are highly prevalent. The incidence of TSIH can exceed 30% in patient cohorts with risk factors who are followed up adequately [5]. Such a prevalent pathology—resulting directly from a surgical intervention—warrants special attention through the development of effective preventive measures.

Current guidelines recommend closing all trocar sites that are 10 mm or larger but there is not enough data on optimal closure technique or material [7]. Some researchers have also suggested the use of prophylactic mesh placement as a strategy to prevent TSIH; however, evidence in the literature remains limited [8–10]. There is a scarcity of comprehensive clinical guidelines or meta-analyses that strongly support these practices. Despite the inconclusive nature of the available data, the most recent joint review by the European Hernia Society and the American Hernia Society provided a “weak recommendation” for placing mesh in the preperitoneal space [7]. Previous investigations have yielded conflicting findings: while several studies from the past decade endorsed sublay mesh placement for hernia prevention [8–10], a more recent study assessing onlay mesh did not confirm its efficacy [11]. Based on these findings, and considering that current incisional hernia guidelines recommend sublay mesh placement [12], we hypothesize that positioning a reinforcing sublay mesh (as opposed to a supra-aponeurotic mesh) at the umbilical trocar site in patients with one or more risk factors could reduce the incidence of TSIH.

Finally, an equally important aspect in our current healthcare context is the rationalization of resources. In an effort to highlight the significance of incisional hernias (IH), increase their visibility, and secure funding for research, Poulose et al. published a study estimating the cost of IH repair: $3,873 for outpatient procedures and $15,899 for inpatient surgeries. The study further determined that each 1% reduction in recurrence rates translates into an annual savings of $32 million in procedural costs alone [13].

In our setting, the Catalan Health Service (Servei Català de la Salut, Catalonia, Spain) published in 2013 the official pricing of public health services, listing the cost of a “hernia surgical procedure, excluding inguinal or femoral hernias, in patients over 17 years old, without complications or comorbidities” at a level III reference hospital as €2,608.35 [14].

A cost–benefit analysis focused on reducing the incidence of TSIH represents a valuable avenue for future research.

The objective of our study is to evaluate the efficacy of prophylactic sublay mesh placement in reducing the incidence of TSIH without increasing morbidity. We hypothesize that sublay mesh placement, due to its morphological characteristics and optimal positioning, may be more effective in preventing TSIH.

Our study will provide Level I evidence (Oxford Centre or Evidence- Based Medicine), as it is designed as a prospective, multicenter, randomized controlled trial with 1:1 allocation and double-blinding of patients and principal investigators. Inclusion criteria have been selected to increase the likelihood that participants present the event of interest, as they must have one or more risk factors. Although this may initially appear to limit the generalizability of the results, these risk factors—such as obesity, diabetes mellitus, and advanced age—are highly prevalent in the general population.

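### The Discussion claims that patients are blinded, but the Blinding section says they are told whether they have a mesh; the trial is single-blind and its patient-reported outcomes are open-label

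*Protocol article*

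**What the plan says.** The protocol article describes blinding in three places.

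- **Discussion**, in the paragraph that justifies the Level I label: the study is a "randomized controlled trial with 1:1 allocation and double-blinding of patients and principal investigators".
- **Blinding**, the section that sets the procedure: "The trial is blinded with respect to the principal investigator". On patients: "Patients are informed about whether a mesh was placed, in accordance with our current protocol". On the assessor: "However, the surgeon (principal investigator) remains blinded during follow-up".
- **Abstract, Methods**: "The principal investigator will remain blinded during follow-up". Patients are not mentioned as blinded.

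On outcomes, the Follow-Up section lists, besides complications, "pain [measured using the Visual Analogue Scale(VAS)], time to return to work, and resumption of daily activities" for each visit. The Data Collection and Analysis section repeats these among the secondary variables and adds emergency department visits. It defines the primary outcome thus: "The primary variable is the occurrence of herniation at the umbilical trocar site (eventration/TSIH").

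**The concern.** One document gives two incompatible accounts of who knows the allocation. The Discussion offers patient blinding as a reason to trust the design, while the procedure tells patients which treatment they had.

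Two things are at stake. First, someone judging risk of bias from the Discussion would credit a safeguard that the trial lacks. That matters most for outcomes that run through the patient's own perception or decisions: a patient who knows that an implant is present may rate pain, judge readiness for work or decide to seek care differently from one who knows there is none. The Discussion states the objective as fewer hernias without added morbidity, so these outcomes bear on the second half of that conclusion. Second, an informed patient is a possible channel by which the blinded examiner could learn the arm.

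**Working it through.** No arithmetic decides this point. The check sets the statements side by side and then traces which outcomes depend on them.

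**Step 1. Who is blinded, by section.**

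| Section | Patient | Principal investigator |
|---|---|---|
| Abstract, Methods | not named as blinded | blinded at follow-up |
| Blinding | told whether a mesh was used | blinded at follow-up |
| Discussion | blinded | blinded |

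The investigator column agrees in all three rows. The patient column does not: the Blinding section and the Discussion cannot both be true.

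**Step 2. Which account governs.** The Blinding section describes what will be done, and the Abstract is compatible with it. The Discussion only characterises the design. No section describes concealing the allocation from patients, a delay before they are told, or a visit at which they are still unaware. On the article's own account, then, patients are unblinded and the follow-up examiner is blinded.

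**Step 3. How many patients.** The disclosure is stated for patients in general, without exception by arm or centre. With the planned 42 per arm, that is 2 × 42 = 84 patients.

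**Step 4. Which outcomes.** The Data Collection and Analysis section lists seven postoperative secondary outcomes: surgical site occurrences, pain, length of stay, emergency department visits, readmissions, return to work and basic daily activities. Four of the seven are reported by the patient or depend partly on the patient's decision: pain, emergency visits, return to work and daily activities.

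**Step 5. The primary outcome.** Hernia is sought by physical examination, by the blinded investigator, before the ultrasound, which a specialised radiologist performs. That order protects the examiner from learning the arm through the scan. It does not address a patient mentioning the arm at a visit where pain and complications are discussed. Such disclosure is possible, but nothing in the article shows how often it would occur or what effect it would have.

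**Step 6. Effect on figures.** The sample size rests on hernia incidence alone (35% against 10%). Correcting the description of blinding changes no figure in the article.

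**The case against.** The strongest reply is that this is one phrase in a Discussion. The Abstract and the Blinding section agree, disclose openly that patients know, and govern conduct. Correcting the phrase alters no procedure, endpoint, sample size or analysis. Telling patients about an implant is a disclosed choice and not in itself an error. The affected outcomes are all secondary, and the article nowhere calls them blinded. All of this stands. It makes the problem one of misdescription and not of faulty design, but it does not make the Discussion sentence true.

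A reader might also draw three stronger conclusions, which the article does not support:

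- *The primary outcome is biased.* It is only exposed to a possible route. The examiner is blinded, the examination comes before the scan, and a radiologist contributes imaging. The article does not say whether the radiologist is blinded, so the risk cannot be called nil, but no bias is shown.
- *The blinding claim fails as a whole.* Only its patient half is contradicted.
- *The Level I label falls.* The Abstract makes the same claim from the prospective, multicentre, randomised design, without mentioning patient blinding as a ground. The false phrase is one listed feature among several.

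It is also fair to say that the article does not state when patients are told, so open-label status at every visit is an inference. It is the natural one, because no delay is described. Finally, a non-disclosure instruction may already stand in the full protocol, which is not shown; its absence from the article is not an error.

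**Conclusion.** The statement that patients are blinded is wrong as written and should be corrected. By its own procedure the trial is single-blind, with the principal investigator blinded at follow-up and patients informed. Four of the seven listed postoperative secondary outcomes are therefore open-label for all 84 planned patients. Neither the direction nor the size of any resulting bias can be derived from the article.

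This assumes that the Blinding section is the operative text and that patients are told before the follow-up assessments. If they were told only later, the earlier visits might be protected, but the article would have to say so. The contradiction itself needs no assumption.

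This is a correction of moderate weight, not a defect that undermines the trial: randomisation, 1:1 allocation and examiner blinding are unaffected, and the threat to the primary outcome through patient disclosure remains a possibility only.

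**What to change.** 1. **Discussion.** Replace the double-blinding phrase with wording such as: single-blind; the principal investigator who examines patients at follow-up is blinded, and patients are not. Keep examiner blinding among the design features that support the Level I claim and remove patient blinding from them.
2. **Interpretation.** State that pain, return to work, daily activities and emergency department visits are open-label comparisons, and interpret them as such when results are reported.
3. **Recommended safeguard.** Unless the full protocol already provides for it, ask patients not to mention their allocation before the physical examination, and record on the visit form whether the examiner became aware of it. This protects the only blinding that the trial has and lets the report show how well it held.

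The cost is a wording change, a sentence on interpretation, one instruction to patients and one form field. The design description becomes less favourable. No treatment, visit, endpoint or sample size changes.
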